## Abstract

**Introduction:** Rehabilitation approaches have been used for people with stroke to decrease spasticity and improve functions, but little is known about the effect of neuromuscular electrical stimulation (NMES) in this population. Therefore, the primary purpose of this study was to establish a protocol for a double-blinded randomized clinical trial to examine using NMES on plantarflexors spasticity, dorsiflexor muscle strength, physical functions, and self-reported health outcomes in people with chronic stroke in Saudi Arabia.

**Material and Methods:** This randomized clinical trial with two arms and double-blinded registered in ClinicalTrials (NCT04673045) will enroll 44 participants with chronic stroke and randomized them into either the experimental group (EG), including electrical stimulation (ES) with conventional therapy or the control sham group (NMES_sham_) including placebo electrical stimulation with conventional therapy. The frequency will be set at 80 Hz for 30 min. The intervention will be three times a week for 4 weeks for both groups. Data collection for pre- and post-intervention outcomes will include measurements for the primary outcomes including paretic limb (plantarflexor spasticity, ankle range of motion, and dorsiflexor muscles strength), and gait speed using 10-m walk test (10-MWT). The secondary outcomes including mobility function using Timed Up and Go (TUG), walking endurance using 6 Minutes Walk Test (6-MWT), activity of daily living using the Arabic version of Barthel Index (BI), and self-reported health measures such as quality of life using the Medical Outcomes Survey (Short Form 36, SF-36), physical activity using Rapid Assessment of Physical Activity (RAPA), depression symptoms using Patient Health Questionnaire-9 (PHQ-9), fatigue level using Fatigue Severity Scale (FSS), and risk of fall using Fall Efficacy Scale International (FES-I). An independent *t*-test will be utilized to examine the effect of the intervention on the outcome measures.

**Results:** The recruitment has started and is ongoing.

**Conclusions:** Using 4 weeks of NMES will provide information about its effect in improving plantarflexor spasticity, dorsiflexor muscles strength, gait speed, mobility functions, and other self-reported health outcomes in people with chronic stroke when compared to NMES_sham_.

## Introduction

Stroke prevalence in Saudi Arabia has been estimated to be 0.67% of the population (1). A recent study showed that the pooled annual stroke incidence was estimated to be 29 cases per 100,000 people in Saudi Arabia (2). However, limited research in Saudi Arabia regarding the impact of stroke on functionality and other outcomes. Stroke is associated with sensorimotor impairments including spasticity, muscle weakness, and deficiency in proprioception, which are serious challenges for clinical treatment for people with stroke. Studies showed that 20–50% of stroke survivors develop spasticity after 6 months of the incidence (3, 4). Spasticity can severely limit functions and negatively impact participation in the community, activities of daily living (ADLs), and quality of life (QoL) (5).

Recently, neuromuscular electrical stimulation (NMES) has been used to inhibit spasticity (6, 7). Yang et al. (6) found that using NMES at tibialis anterior (TA) for 20 min followed by ambulation training reduced the spasticity of ankle plantarflexors. Sabut et al., (8) found that using functional electrical stimulation (FES) on the TA showed an improvement in plantarflexor spasticity by 38.3% and increased dorsiflexor muscle strength by 56.6% compared to conventional rehabilitation program (CRP) in people with stroke (8). However, there are controversial studies that did not find improvement after using electrical stimulation on the spasticity level (9, 10).

A previous meta-analysis has examined the effect of NMES on spasticity for people with stroke. This study included 29 clinical trials and found that NMES was associated with a greater reduction in spasticity. However, this study included reports with upper and lower extremities, and none of the lower extremity studies blinded the participants (11). The limitations of the previous studies were the small sample size, different stimulation time and frequency, and lacking a sham comparison group.

Using a sham NMES would have less bias and more accuracy in the findings taking into consideration the Hawthorne effect or placebo effect, especially when using electrical modalities. Furthermore, the effect of using electrical stimulation within a rehabilitation approach in Saudi Arabia is very limited, requiring further research. Thus, a treatment program with a placebo control (sham NMES, NMES_sham_) may have a better estimate on its effect on ankle plantarflexors spasticity in people with chronic stroke living in Saudi Arabia.

Therefore, the primary purpose of this study was to evaluate the effect of using NMES on spasticity of the ankle plantarflexors, ankle range of motion (ROM), dorsiflexors strength, and gait speed in people with chronic stroke. The secondary purpose of this study was to explore the effect of using NMES on mobility function and physical performance measures including walking endurance and ADL and self-reported health measures including QoL, physical activity, depression symptoms, fatigue, and risk of fall in this population.

## Materials and Methods

The protocol was developed according to the Standard Protocol Items: Recommendations for Interventional Trials (SPIRIT) guidelines and checklists.

### Study Design

This study is a two-arm, parallel, double-blinded, single-site, randomized clinical trial (RCT) with two independent variables, between-subject factor (group), and within-subject factor (time). The independent variable of groups has two levels: active NMES (experimental group) and placebo group. The independent variable of time has two levels: baseline (T_0_) and post-intervention (T_1_). The participants will be assigned randomly on a 1:1 ratio into either the experimental group (EG) or to the placebo group (NMES_sham_). Outcomes assessor and participants are blinded to the allocation of groups.

### Study Setting

This study will be conducted at the physical therapy department, King Fahad Specialist Hospital, Buraydah, Saudi Arabia.

### Registry of Clinical Trials

The study protocol was registered in ClinicalTrials (registration number NCT0467304).

### Participants and Recruitment

About 44 men and women of any race or ethnicity with a brain stroke will be recruited in the Qassim area to participate in this study based on a previous study (7). The participants will be recruited through advertising in the local communities, health professionals, family members, and support groups. Prior to any testing or data collection, all of the participants will read and sign an informed consent form describing this study approved by national bioethics committee review boards in Saudi Arabia. Upon entry into the study, the principal investigator (PI) or the co-investigators will explain the research project to the participants and inform them of the risks and benefits of the study. Then, a questionnaire of demographic and medical history information will be obtained. Participants will be screened by an experienced assessor for eligibility to participate in this study. The timepoints for recruitment, assessments, and interventions are shown in Figure 1.

**Figure 1 F1:**
[figure not shown]
Standard Protocol Items: Recommendations for Interventional Trials (SPIRIT) for the content of the schedule of enrolment, interventions, and assessments checklist.

#### Ethical Approval

The study protocol is approved by the national bioethics committee review boards of the Ministry of Health, Saudi Arabia (1442-551803). All participants give written informed consent prior to the study enrollment.

#### Inclusion Criteria

Participants will be included if they had a first incident of brain stroke aged from 18 to 65 years old and have at least 6 months since stroke to avoid the effects of spontaneous recovery. Independent ambulatory ability with or without assistive device at least 10 m (e.g., cane and walker), plantarflexors spasticity on paretic limb ≥2 on modified Ashworth scale (MAS) (12), and functional ambulation ≥3 on functional ambulation categories (13).

#### Exclusion Criteria

Participants will be excluded from the study if they did not meet the inclusion criteria. Furthermore, participants will be excluded if they have skin integrity issues on contact surface of NMES, significant cognitive impairments (unable to follow three step commands), other serious medical conditions, history of other neurologic or orthopedic disorder affecting walking function, more than one previous stroke, contraindications to NMES, such as a pacemaker or tumor, injected with any medicine that reduce spasticity (e.g., Botulinum-A Toxin), pregnancy, and previous lower limb treatment with FES or NMES.

### Outcome Measures

Primary and secondary outcome measures will be collected by a blinded trained assessor at the baseline and after the intervention (4 weeks of intervention). Primary outcomes will include spasticity in the plantarflexor muscles in paretic leg measured by MAS, active and passive ROM for the ankle joint in paretic leg measured by a handheld goniometer, muscle strength for the ankle dorsiflexor muscle in paretic leg measured by manual muscle testing (MMT), gait speed using 10-meter walk test (10-MWT). Secondary outcome measures will include mobility function using Timed Up and Go (TUG), walking endurance using 6 MWT, ADL using the Arabic version Barthel index (BI), and self-reported health measures such as Medical Outcomes Survey (Short Form-36, SF-36), physical activity using RAPA, depression symptoms using Patient Health Questionnaire-9 (PHQ-9), fatigue level using the Arabic version of Fatigue Severity Scale (FSS), and risk of fall using the Arabic version of Fall Efficacy Scale International (FES-I).

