##### Active and Passive Range of Motion

The test consists of active and passive ankle joint ROM. The measurement will be in degrees using a handheld goniometer. Goniometry will be performed with the subject in a supine position with extended knees, and the measurement will be made at the neutral position between dorsal flexion and plantar flexion. The axis of the goniometer will be placed 2 cm below the medial malleolus, and its moving axis will be placed along the first metatarsal bone. The passive ROM will be determined as the range that the assessor is able to move the subject's ankle beginning in maximum plantarflexion to maximum dorsiflexion until any resistance is felt. Similarly, the active ROM will be measured by asking the participants to move joints maximally. The test will be performed at the baseline and post-intervention. Three measurements for the active and passive ROM will be taken, and the average will be calculated for the ankle dorsiflexion ROM.

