### Statistical Analysis

IBM SPSS Version 25.0 (IBM Corp., Armonk, NY, USA) will be used to analyze the collected variables. The descriptive demographic information (means, medians, and SD) include age, gender, onset of the stroke, height, weight, and all outcome measures will be calculated and compared at the baseline using the independent *t*-test or chi-square test to ensure that there is no significant difference between the two groups at the baseline. Normality of the data will be assessed using the Shapiro–Wilk test. Comparisons between pre- and post-intervention will be conducted using the dependent *t*-test or the Wilcoxon signed rank test to determine if there will be significant differences between two different timepoints for each group. The independent *t*-test or the Mann–Whitney *U*-test will be used to compare the recorded values at the post-intervention between the two groups. In case of confounding variables such as age, secondary analysis will be performed according to the age groups (18–30, 31–50, and 51–65 years). In order to account for pre- and post-intervention between-group clinical effectiveness in terms of the outcome measures, Cohen's *d* effect size will be calculated. Furthermore, the pre-test effect sizes will be subtracted from the post-test effect sizes to effectively control for the differences at the baseline and obtain the absolute effect size. Effect sizes will be defined as small (*d* ≤ 0.2), medium (0.2 > *d* < 0.8), and large (*d* ≥ 0.8) (43). Differences will be considered statistically significant when *p* < 0.05.

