## Discussion

The main objective of this clinical trial is to evaluate the effect of using NMES on plantarflexor muscle spasticity, ankle ROM, dorsiflexor muscle strength, and gait speed. The secondary objective of this work is to examine the effect of using NMES on mobility function, walking endurance, and self-reported outcomes such as ADL, QoL, physical activity, depression symptoms, fatigue level, and risk of fall.

The findings from this study will highlight the importance and effect of using electrical stimulation during a rehabilitation program for individuals with chronic stroke living in Saudi Arabia. If the findings are positive, this study will be the first that has preliminary positive results for a rehabilitation program using NMES in this population in Saudi Arabia. The results will eventually help healthcare providers and other researchers in choosing and investigating the appropriate rehabilitation approach to improve spasticity and functionality.

Upon completion of data collection, it is expected that the active NMES group will benefit from decreased ankle plantarflexors spasticity, increased dorsiflexors strength, and improved walking function, physical activity, and QoL. The placebo group will gain benefit from CRP; however, it is expected that the scores of placebo group in targeted outcomes will show less variation than EG. The result will be published after the data and the study is completed.

Although this study has some strengths including blinded assessors, blinded participants, and placebo NMES to decrease bias, there are some limitations. A single center study is a possible limitation that may limit the generalizability of the results. Using a clinical setting (hospital outpatient clinic) with lack of tools is another limitation that may limit the use of objective tools such as EMG. Drop out is another limitation that may occur in clinical trials that affects sample size and results. Lack of follow-up assessment after the intervention is another limitation due to limited financial resources that affect the results of long-term effect and persistence of the results of this treatment.

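### Five primary variables are each judged at p < 0.05 with no stated success rule: if any one positive result counts, the familywise error is about 10–23%, not 5%

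*Protocol article*

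**What the plan says.** The Outcome Measures section of the protocol article begins its primary list with "Primary outcomes will include spasticity in the plantarflexor muscles in paretic leg measured by MAS, active and passive ROM for the ankle joint" and continues with "muscle strength for the ankle dorsiflexor muscle in paretic leg measured by manual muscle testing (MMT), gait speed using 10-meter walk test (10-MWT"). The section on range of motion treats the active and passive measurements as two quantities: "The test consists of active and passive ankle joint ROM". The primary set is therefore five variables: MAS, active ROM, passive ROM, MMT and 10-MWT speed. It covers four domains if the two ROM measures are counted as one.

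The list is not a slip in one sentence. The Abstract and the end of the Introduction give the same domains as primary, and the Discussion states the main aim as to "evaluate the effect of using NMES on plantarflexor muscle spasticity, ankle ROM, dorsiflexor muscle strength, and gait speed".

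For the comparison of arms, Statistical Analysis says: "The independent *t*-test or the Mann–Whitney *U*-test will be used to compare the recorded values at the post-intervention between the two groups". The only decision rule is "Differences will be considered statistically significant when *p* < 0.05". Nowhere does the article put the primary outcomes in order, divide the significance level, or say whether one, some or all of them must be positive. Sample Size Calculation refers to a previous study and does not say which outcome the 44 participants were sized for.

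**The concern.** A 0.05 threshold limits the false-positive risk of one test. With five primary tests and no rule for combining them, 0.05 is not necessarily the error rate of the claim a reader will take away, namely that NMES works. A lone significant result on, say, passive ROM could be reported as a positive primary finding, with nothing in the plan to say whether it is one.

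The plan also gives no answer when results are mixed, for example if ROM improves while spasticity and gait speed do not. The Discussion anticipates positive findings and expects them to guide the choice of rehabilitation approach, but does not define what would count as positive. A rule chosen after the results are known would carry little weight.

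**Working it through.** **Inputs from the article.** Five primary variables (Outcome Measures; Active and Passive Range of Motion). One between-group test per outcome at post-intervention, each at 0.05 (Statistical Analysis). 22 per arm and 10% attrition (Allocation Sequence Generation; Sample Size Calculation).

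**Assumptions.** Two-sided tests, because sidedness is not stated. Correlation between the test statistics, because none is given. Success defined as at least one positive primary outcome, because no rule is given.

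**The plan's own figures.** The article states no familywise rate. Its only error rate is 0.05 per test, which is correct for a single primary outcome: 1 − 0.95 = 5%. The sample size cannot be rebuilt, since its effect size, SD, power and outcome are not reported. The calculation below does not need them.

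**Independent tests.** Familywise error = 1 − (1 − 0.05)^k.
- k = 5: 1 − 0.95^5 = 1 − 0.7738 = 22.6%.
- k = 4 (ROM counted once): 1 − 0.95^4 = 1 − 0.8145 = 18.5%.

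**Correlated tests.** For k equicorrelated normal statistics with common correlation ρ and c = 1.96, familywise error = 1 − ∫ φ(u) [Φ((c − √ρ·u)/√(1 − ρ)) − Φ((−c − √ρ·u)/√(1 − ρ))]^k du. Numerical integration gives:

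| Assumed ρ | Five tests | Four tests |
|---|---|---|
| 0 | 22.6% | 18.5% |
| 0.3 | 20.9% | 17.4% |
| 0.5 | 18.3% | 15.6% |
| 0.7 | 14.8% | 13.0% |
| 0.9 | 10.2% | 9.4% |

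**Unequal correlation.** With active and passive ROM correlated at 0.8 and all other pairs at 0.3, simulation of five tests gives 19.7%. With the other pairs at 0.5 it gives 17.5%.

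**After correction.** Bonferroni at 0.05/5 = 0.01 gives 1 − 0.99^5 = 4.9% under independence. Holm keeps the familywise rate at or below 5% whatever the correlation. Its successive thresholds are 0.01, 0.0125, 0.0167, 0.025 and 0.05.

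**Power cost.** 22 × 0.9 = 19.8, so about 20 per arm complete. For a two-sample t-test (noncentral t, 38 degrees of freedom), the standardised difference detectable with 80% power is d = 0.91 at 0.05 and d = 1.13 at 0.01. At the intermediate Holm thresholds it is 1.10 (0.0125), 1.06 (0.0167) and 1.01 (0.025).

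**The case against.** **The decision rule is not stated.** The inflation arises only if any one positive outcome is enough. The article lists the domains jointly and expects benefit across several of them. If all five had to be positive, the type I error would be at most 5% with no adjustment, and the difficulty would be power. This stands: a reader might infer that the trial's false-positive rate simply is 18–23%, but the article supports that figure only under the any-one reading and with correlations of at most about 0.5.

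**The outcomes may be strongly correlated.** MAS and passive ROM are both assessed by moving the ankle passively towards dorsiflexion, and active ROM and MMT both depend on dorsiflexor action. This also stands and is why the range must extend down to about 10%. Ties in the ordinal MAS and MMT could lower the rate slightly further. No case tried comes near 5%.

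**A fuller analysis plan may hold the rule.** It may, so the point is that none is stated here, not that no adjustment will be made. The objection does not remove the point, because the article itself fixes both the primary set and the threshold, and together these leave the primary claim undefined.

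**Two further inferences go too far.** Counting all 13 named outcomes gives 1 − 0.95^13 = 49% if independent, but eight of those are declared secondary and do not bear on the primary claim. It is also tempting to conclude that MAS must be the sole primary outcome, since it is listed first and is an entry criterion. The article does not compel that choice, because it does not say which outcome determined the sample size.

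**Conclusion.** The point holds in conditional form. The article declares five primary variables, judges each at p < 0.05, and states no success rule, ranking or adjustment. If any one positive result is taken as evidence that NMES works, the familywise error is roughly two to four and a half times the nominal 5%: from 10.2% at an assumed common correlation of 0.9 to 22.6% under independence. Counting ROM once lowers this to 9.4–18.5%.

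These figures cover only the five between-group comparisons at post-intervention. The within-group pre-post tests and the age-group analyses come under the same threshold and are not counted.

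**What to change.** Before unblinding, amend Statistical Analysis so that the five primary between-group comparisons are tested with Holm at a familywise level of 0.05, and state that a claim on any primary outcome rests on the Holm-adjusted result. Alternatively, name one primary outcome, consistent with the outcome used for the sample size, and make the other four secondary. Under either option, describe the secondary outcomes as supportive.

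The change needs a protocol and registry amendment but no new data. The Abstract says recruitment is still under way.

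The cost of Holm is power. The smallest p-value must be at most 0.01, which gives the rise from d = 0.91 to d = 1.13 calculated above. That is the worst case for one outcome, since later steps are less strict. It also assumes a t-test, whereas MAS and MMT may be analysed with the Mann–Whitney test. Naming a single primary outcome keeps d = 0.91 for that outcome but demotes four that have already been declared primary.

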#### Primary Outcome Measure Procedures

##### Demographic and Clinical Variables

The diagnosis, age, sex, marital status, education, employment, self-reported comorbidities such as diabetes and hypertension, self-reported medications, self-reported history of falls in the past 12 months, self-reported pain in the past month, and body mass index using weight (kg) and height in (cm) will be obtained at the baseline session. The diagnosis of stroke includes location of injury, stroke type, artery infarction, side of the body paralysis, dominant side, and duration of the stroke.

##### Modified Ashworth Scale

The spasticity in the plantarflexor muscles tone will be measured on the affected leg using MAS. Participants will be placed in a supine position. To test ankle plantarflexor muscles' spasticity, from maximal ankle plantarflexor position, the assessor passively moves the ankle to maximal dorsiflexion position over 1 s. The test will be performed at the baseline and post-intervention. Spasticity will be graded according to MAS, which is a 6-point rating scale (12):

0 No increase in muscle tone.1 Slight increase in muscle tone, manifested by a catch and release or by minimal resistance at the end of the ROM when the affected part(s) is moved in flexion or extension.1+ Slight increase in muscle tone, manifested by a catch, followed by minimal resistance throughout the remainder (less than half) of the ROM.2 More marked increase in muscle tone through most of the ROM, but affected part(s) easily moved.3 Considerable increase in muscle tone, passive movement difficult.4 Affected part(s) rigid in flexion or extension.

